### Cost-effectiveness evaluation

In the cost-effectiveness analysis, the evaluation will be performed from the perspective of the payer (i.e. the NHS), as advocated by the National Institute for Health and Clinical Excellence (NICE) [30], hence the evaluation will focus on additional direct healthcare costs incurred as a result of MRSA colonization. Collection of all resource use data will take place continuously throughout the study period. Patient-specific direct healthcare resource use (such as additional ICU days, antibiotic consumption, additional contact precautions, laboratory tests) will be collected alongside the RCT for both control and intervention groups, and supplemented with standardized unit cost data [31]. We will also record TISS (Therapeutic Intervention Scoring System) data. TISS is recognized and used worldwide as an indicator of the amount of care invested for a particular patient over an agreed time period. The score is a set of selected therapeutic activities among the many activities performed in ICUs. No attempt will be made to quantify non-healthcare costs, costs incurred by the patient, and costs associated with the rise of antibiotic resistance, as this is beyond the remit of the current evaluation.

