## Background

Over the past ten years there has been a dramatic increase in the number of infections caused by MRSA in several countries, including the United Kingdom (UK) [1]; this pathogen is now endemic in hospitals throughout the country. It appears that although many patients begin by being colonized, without any clinically evident infection, between 30% and 60% of colonized critically ill patients subsequently develop an infection syndrome attributable to the organism [2,3]. In fact, colonization pressure (number of MRSA carrier patient-days/total patient-days) is a major independent predictor of MRSA infection in a given critically ill population [4].

MRSA infection appears to be associated with greater attributable mortality than infection with methicillin-sensitive Staphylococcus aureus (MSSA), based on a recent meta-analysis of bacteraemia outcomes [5], although this may reflect the vulnerability of the patient population infected by MRSA, rather than greater virulence of the organism *per se*. Nevertheless, compared to MSSA, infections with MRSA demand treatment with antimicrobial agents of greater toxicity and acquisition costs; many of these drugs also require frequent monitoring of serum levels, further adding to the total cost of therapy [1,5]. Moreover, MRSA infection is associated with prolonged length of hospital stay, including duration of Intensive Care Unit (ICU) stay; using data from the National Audit Office, nosocomial infection is estimated to be associated with, on average, 11 additional days in hospital and total costs of 2.8 times that of uninfected patients [6-10]. Indeed, even without progression to infection, colonized patients require increased healthcare resource in the numerous measures implemented to limit the spread of MRSA to other patients. Investigators in Canada, using a cost model, estimated the additional cost per patient episode arising from MRSA colonization (without infection) equivalent to £650 [11]. Applying these costs to local ICU surveillance data, new MRSA colonization alone may add around £65,000 per annum to cost of care in a 17-bed ICU, aside from costs of prolonged ICU stay.

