End-of-study screening specimens will be obtained from all participants on ICU discharge or death to identify those patients in whom MRSA acquisition has occurred during the inpatient episode. Additional information regarding MRSA acquisition as a result of MRSA detection in other clinical specimens taken as part of routine care in the ICU will also be recorded. The time of swab collection will be recorded.

Quantity of body wash will be determined by counting the number of bottles used. Antibiotic consumption will be retrieved from prospectively generated computerized patient records. Compliance and adverse effects will be monitored daily by incorporating a record of washing (including time of washes) and adverse events in standard nursing records.

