#### Hypothesis 2: Cost-effectiveness analysis

Consistent with NICE recommendations, resource use and unit cost data will be presented separately, in £Sterling (2007); discounting of costs and outcomes at 3.5% per annum will be performed. Statistical analyses will be performed to examine differences in costs between groups and bootstrapping will be undertaken to allow for the skewed distribution of costs. Variability in cost-generating events will be examined by calculating the variance/mean ratio, and variability in costs examined by calculating the coefficient of variation. An incremental cost-effectiveness ratio (ICER) will be calculated, which is defined as the change in costs over the change in effect: ICER = Δc/Δe. The ICER (and 95% confidence ellipses) will be presented on the cost-effectiveness plane. Uncertainty relating to the data used in the analysis, methodological assumptions and the need to extrapolate the data or generalize to other settings will be addressed by decision analytic modelling and a range sensitivity analysis performed to determine the extent of uncertainty in point estimates.

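### The cost scope is tied to the consequences of MRSA colonization and, read literally, leaves the allocated wash out of the ICER numerator

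*Protocol article*

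**What the plan says.** The scope is set in the protocol article under Cost-effectiveness evaluation. After adopting the NHS payer perspective, the section continues: "hence the evaluation will focus on additional direct healthcare costs incurred as a result of MRSA colonization". Its examples of patient-level resource use are given as "such as additional ICU days, antibiotic consumption, additional contact precautions, laboratory tests".

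The same section says "Collection of all resource use data will take place continuously throughout the study period", and that patient-specific data "will be collected alongside the RCT for both control and intervention groups, and supplemented with standardized unit cost data". It then names what is left out: "No attempt will be made to quantify non-healthcare costs, costs incurred by the patient, and costs associated with the rise of antibiotic resistance".

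Under Hypothesis 2: Cost-effectiveness analysis, costs are compared between groups with bootstrapping. The ICER is introduced there as a ratio "which is defined as the change in costs over the change in effect", without listing the components of cost.

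Bottle use is recorded under Data collection methods and assessments: "Quantity of body wash will be determined by counting the number of bottles used". Table 1 repeats that item and also lists adverse events. The data collection section includes length of ICU stay among the risk factors for MRSA to be analysed as covariates. Under Outcome measures, the economic outcome is the cost saving per colonization avoided.

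**The concern.** A payer perspective decides whose costs count. It does not restrict those costs to one causal pathway. The wash is bought for every randomised patient whether or not colonization occurs, so it is not a cost caused by colonization, and the same holds for treating a reaction to the wash. None of the four resource examples is the intervention itself. The Hypothesis 2 section does not define costs again, so an analyst who wants a definition has only the scope sentence.

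There is a second difficulty with the ICU days. If they count only when MRSA caused them, someone has to separate days due to MRSA from days that would have occurred anyway. The protocol also treats length of stay as a risk factor for acquiring MRSA, so part of any association between colonization and stay may run from stay to colonization. A comparison of randomised arms needs no such separation.

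At stake is the secondary hypothesis that TTO is the more cost-effective wash. Two analysts could follow the same text, one costing the wash and one not, and report different ICERs, possibly of opposite sign.

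**Working it through.** **1. Inputs.** Control colonization rate 13%, difference 40%, 540 per group, 80% power, two-sided 0.05 (Participants and sample size). Cost per colonization £650 (Background: "estimated the additional cost per patient episode arising from MRSA colonization (without infection) equivalent to £650"). No price is given for either wash, so the extra cost per TTO-arm patient (wash plus adverse effects) is an unknown, *w*.

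**2. Reading of the 40%, checked against the stated sample size.** Taken as relative, the TTO rate is 0.13 × (1 − 0.40) = 0.078. With pooled variance and no continuity correction:

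n = [1.960 × √(2 × 0.104 × 0.896) + 0.842 × √(0.13 × 0.87 + 0.078 × 0.922)]² / 0.052² ≈ 540 per group, 1080 in total.

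This reproduces the plan's figure, so 13% versus 7.8% is the design contrast.

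**3. Saving from avoided colonization.** Risk difference = 0.13 − 0.078 = 0.052. Saving per patient = 0.052 × £650 = £33.80. Among 540 patients, 540 × 0.052 ≈ 28 cases are avoided.

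**4. ICER with and without the extra cost.** Change in cost = *w* − 650 × 0.052. Change in effect = 0.052 cases avoided per patient. Hence ICER = *w*/0.052 − 650. Each £1 of *w* left out moves the ICER by 1/0.052 = £19.23 per case avoided.

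| Assumed *w* per patient | Change in cost | ICER per case avoided |
|---|---|---|
| £0 | −£33.80 | −£650 |
| £5 | −£28.80 | −£554 |
| £10 | −£23.80 | −£458 |
| £20 | −£13.80 | −£265 |
| £33.80 | £0 | £0 |
| £50 | +£16.20 | +£312 |
| £100 | +£66.20 | +£1,273 |

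A costing that counts colonization consequences only reports the first row whatever *w* is.

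**5. Dependence on the effect.** The break-even *w* is 650 × 0.13 × relative reduction: £33.80 at 40%, £25.35 at 30%, £16.90 at 20% and £8.45 at 10%.

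**6. Limits of the illustration.** The £650 comes from a Canadian cost model for colonization without infection. The Background describes the annual cost it derives from that figure as separate from prolonged ICU stay, and puts progression from colonization to infection at 30% to 60% in the critically ill. Savings from avoided infection or ICU days would raise the break-even. The trial plans patient-level costing and does not say it will use £650 as an input.

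**The case against.** The strongest reply is that nothing in the article excludes the wash. The scope sentence speaks of a focus, the resource list is open, all resource use is to be collected in both arms, and the named exclusions mention neither the wash nor adverse effects. Bottles are counted, adverse events are recorded, and the ICER rests on cost differences between groups. A journal article may also leave an itemised cost list to the full protocol.

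Much of this stands. A reader might infer that the ICER certainly omits the wash and so makes TTO look cheaper by construction. The documents do not support that. The broader reading is open, no prices are stated, and a tilt towards TTO requires TTO to be the dearer product. Nor is any procedure described for attributing ICU days to MRSA; in a comparison of arms, additional days could simply mean the difference. The adverse-effect component is probably small, since the section on risks describes such effects as minor and uncommon, and extra days, antibiotics or tests they caused would be captured as resource use in both arms.

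What the reply does not remove is the scope sentence itself. It is a stated rule, not an omitted detail, and it does not follow from the payer perspective. Counting bottles shows that the wash could be costed. Neither that section nor Table 1 links bottles to a unit price or to the economic analysis.

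**Conclusion.** The concern holds as a badly fixed scope rule. Followed literally, the sentence leaves the allocated wash and adverse-effect treatment out of the change in costs and ties ICU days to MRSA. The surrounding text is ambiguous enough that this is the literal reading and not an established omission.

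Any bias towards TTO is conditional on TTO costing more than the standard wash; its size and direction cannot be derived from the article. The £33.80 break-even and the £19.23 shift per £1 rest on the design effect being realised and on a background figure that leaves out infection and prolonged ICU stay. They show that the choice of scope can matter to the answer, not that it has distorted it. The scope should be settled before analysis because it bears directly on a stated secondary hypothesis.

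**What to change.** Replace the scope sentence with wording such as: *The change in costs will be the difference between randomised arms in mean total NHS direct cost per analysed randomised patient, including the allocated body wash (bottles used × unit price) and treatment of adverse effects, without attribution to MRSA, over the period for which resource use is collected, including hospital stay to discharge.* State in the Hypothesis 2 section that this quantity is the ICER numerator. Keep MRSA-attributed costs as a descriptive breakdown.

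Costing should not stop at ICU discharge: Table 1 collects hospital length of stay, and those days fall on the same payer.

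The change is mostly wording. Table 1 already has bottles used, ICU and hospital length of stay, TISS, antibiotics, cultures and adverse events. It does not itemise resources used to treat adverse events, so the plan should say how these are costed. It should also say which randomised patients are analysed, because participation can end after a positive pre-intervention screen or declined consent. The statistical price is that total costs vary more than attributed costs, so the interval for the cost difference will be wider.

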### Schedule for assessments

Table 1 demonstrates the schedule for assessments to be performed at given time periods. Data for the previous 24-hours will be collected between 8 am and 10 am. The baseline assessment serves two purposes – first to ensure that patients recruited to the trial meet the inclusion criteria, and second to obtain baseline measures. Trial specific data will be collected in a Case Report Form for source data verification.

**Table 1 T1:** Timing of assessments

	Baseline	Day 1 to *n*	Day *n *(ICU discharge)	Hospital discharge
Inclusion/exclusion criteria	*			
Demographics	*			
APACHE II score	*			
SOFA score	*	*	*	
TISS score		*	*	
Isolation	*	*	*	
Steroid use	*	*	*	
Antibiotic list	*	*	*	
Invasive devices list	*	*	*	
Colonisation data	*	*	*	
Infection data	*	*	*	
No. of cultures sent to laboratory	*	*	*	
Adverse events		*	*	
Whether neighbouring patient has MRSA		*	*	
Standard groin swab	*		*	
Standard nasal swab	*		*	
PCR groin swab (Belfast HSCT)	*			
PCR nasal swab (Belfast HSCT)	*			
Details of wash	*	*	*	
No of body wash bottles used		*	*	
Duration of ventilation			*	
ICU length of stay			*	
ICU survival			*	
Hospital length of stay				*
Hospital survival				*
Discharge location				*

APACHE II – Acute Physiological & Chronic Health Evaluation II; HSCT – Health and Social Care Trust; ICU – Intensive Care Unit; MRSA – Methicillin-resistant Staphylococcus aureus; PCR – Polymerase chain reaction; SOFA – Sequential Organ Failure Assessment; TISS – Therapeutic Intervention Scoring System;

### Statistical analyses

#### Hypothesis 1: TTO evaluation

For continuously distributed outcomes, differences between groups will be tested using independent samples t-tests, analysis of variance (ANOVA) and analysis of covariance (ANCOVA) with transformations of variables to normality if appropriate, or non-parametric equivalents. Chi-square tests (or Fisher's Exact tests) will be used for categorical variables. Major risk-factors for MRSA will be analyzed as covariates. Efficacy of intervention will be analysed on an intention to treat basis. A P value of ≤ 0.05 will be considered significant. A single final analysis is planned at the end of the trial.

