### Design and setting

This multicentre phase II/III prospective, open-label, randomized controlled clinical trial tests the effect of 5% TTO body wash versus standard body wash for prevention of MRSA colonization in critically ill adults. The study is being undertaken in two ICUs in two Health and Social Care Trusts (HSCT) in Northern Ireland. The Regional Intensive Care Unit (RICU) at the Belfast HSCT is a 17-bed intensive care unit (ICU) which receives general medical and surgical patients as well as patients both from regional specialty departments of the Royal Hospitals and from district general hospitals requiring level 3 care. The ICU at the South Eastern HSCT at the Ulster Hospital site is a 10-bed critical care unit which receives general medical and surgical patients requiring level 2 and level 3 care.

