### Participants and sample size

All patients admitted to the ICUs during the study period will be eligible for inclusion in the study except those patients who fulfil the following exclusion criteria: less than 18 years of age; known to be colonized with MRSA at the time of admission; on admission, are judged as unlikely to remain in the ICU for at least 48 hours; are recruited, but whose pre-intervention MRSA screening tests are subsequently found to be positive (by standard culture); consent declined; and have a known sensitivity to TTO.

The primary outcome measure is the difference in MRSA colonization between groups at ICU discharge. The incidence of MRSA colonization during ICU admission in the study population is 13% (data obtained from the feasibility study conducted in one of the ICUs). A sample size of 1080 subjects (540 in each group) will have 80% power at a two-tailed significance level of 0.05 to detect a clinically significant difference of at least 40% in efficacy between 5% TTO and standard body wash. As the study will be confined to ICU, with nursing staff administering the study treatment, compliance will be guaranteed. Given the intensive monitoring in ICU, we do not expect any loss to follow-up.

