### Recruitment of patients, randomisation and consent

When a patient is admitted, the investigator will contact the on-line randomization centre in the Clinical Research Support Centre [a centre providing design, management and coordination services for clinical trials and other studies conducted within the Health and Personal Social Services in Northern Ireland and funded by the Research and Development Office, Northern Ireland]. The investigator will complete the screening form on-line and this will generate a screening number indicating whether the patient is randomized or excluded. The randomization centre will provide the investigator with the allocation to receive either intervention A or B. The investigator will then obtain the appropriate intervention for the patient, which will be stored on the ICU. A record of all patients not randomized, including the reason for not being recruited, will be maintained by the investigator.

As patients are at risk from immediate exposure to MRSA from admission to the ICU, the success of this study will be dependent on randomizing patients as soon as possible. Furthermore as patients will be critically ill, they will not have the capacity to be able to give or withhold informed consent. Delay in recruiting patients would mean a significant proportion of patients would be excluded. Therefore, as the intervention is low risk, we plan to randomize patients on admission and obtain prospective/retrospective consent from their legal representative as soon as possible. In addition, retrospective consent will be obtained from the patient as soon as they are competent. This approach has previously been adopted in trials in the critical care setting [19-21]. In line with The Medicines for Human Use (Clinical Trials) Regulations 2004 and to comply with the Research Governance Framework, consenting processes will be standardised, and reinforced via training prior to study start-up. The planned flow of patients through the study is illustrated in Figure 1.

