### Data collection methods and assessments: TTO evaluation and PCR verification

Data will be collected in a standardized manner across both sites according to Standard Operating Procedures. In both sites, patients will have screening specimens for MRSA carriage (using conventional culture methods on nasal and groin samples) carried out as a component of routine care by the nurse responsible for their care on admission to the ICU. For pragmatic reasons, duplicate specimens for processing by the PCR assay will only be taken in the RICU in the Belfast HSCT. All specimens will be obtained prior to either intervention commencing and will consist of swabs from both the nose and groin of all patients. Patients whose admission screening is positive by either method will be removed from the study (see exclusion criteria).

To facilitate verification of the PCR assay in the Belfast HSCT study population, its results will be compared to the culture results. Where there is disagreement between the culture and PCR results both will be repeated. In instances when the culture is persistently positive but the PCR assay persistently negative, this will be recorded as a false-negative PCR result (assuming a true-positive culture result). In instances when the culture result is persistently negative but the PCR assay is persistently positive, this will be recorded as a true-positive PCR result (assuming a false-negative culture result). If either test is not consistently positive or negative, it will be recorded as equivocal.

The presence of established major risk-factors for MRSA will be recorded, so that each can be analyzed as a covariate. These are:

• Total number of antibiotic-days during the ICU episode [24-26].

• Age (blocked by 10-year intervals).

• Number of comorbidities

• Intravascular catheter-days (number of devices × number of days) [27,28].

• Length of ICU stay [28,29].

• Severity of illness on admission to ICU [29].

Several other MRSA risk factors exist, such as transfer from high prevalence clinical units, multiple prior hospitalizations and residence in a nursing home. However, if participants are culture-negative at the time of admission to ICU, then these factors are not significant and therefore will not be recorded.

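### The stated covariate list leaves out ICU and bands age, and the named test for the primary outcome is unstratified: a small, free gain in precision is forgone

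*Protocol article*

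**What the plan says.** Under Hypothesis 1: TTO evaluation, the protocol article assigns chi-square or Fisher's exact tests to categorical variables and adds: "Major risk-factors for MRSA will be analyzed as covariates". It does not say whether the covariate analysis or the simple test is the primary comparison.

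The section on data collection methods and assessments names the factors: antibiotic-days in the ICU episode, age, number of comorbidities, intravascular catheter-days, length of ICU stay, and severity on admission. Age is entered as "Age (blocked by 10-year intervals" (the closing bracket follows). The same section explains why some other risk factors are not recorded. ICU appears neither among the six nor among those set aside.

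On setting, Design and setting states: "The study is being undertaken in two ICUs in two Health and Social Care Trusts". It describes a 17-bed regional unit receiving specialty and district referrals needing level 3 care, and a 10-bed unit receiving general patients at levels 2 and 3. The 13% control rate under Participants and sample size rests on "data obtained from the feasibility study conducted in one of the ICUs".

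On allocation, the recruitment section says: "The randomization centre will provide the investigator with the allocation to receive either intervention A or B". It does not mention stratification by unit.

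**The concern.** Unit is known for every patient at randomisation and plausibly predicts the outcome. The two ICUs differ in size, referral pattern and level of care. The Background also names colonization pressure, which is a property of the unit, as a major predictor of MRSA infection. The other unit's colonization rate is not given, so equal rates cannot be assumed.

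If the rates differ and unit is ignored, a chance excess of one unit's patients in one arm moves the crude difference, and nothing in the stated analysis removes that movement. If randomisation is in fact stratified by unit, the imbalance is controlled by design, but an unstratified test then uses a standard error that is slightly too large.

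Banding age discards variation within each band. If the bands enter as categories, they also use several parameters where one might do. What is at stake is precision and the robustness of one trial's result to chance imbalance, not validity.

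**Working it through.** **1. Reproduce the plan's figure.** The plan states: "A sample size of 1080 subjects (540 in each group) will have 80% power at a two-tailed significance level of 0.05". The planned effect is given as 40%. Reading this as a relative reduction, p1 = 0.13 and p2 = 0.13 × 0.6 = 0.078. The difference is 0.052 and the mean rate is 0.104.

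n per arm = [1.96·√(2·0.104·0.896) + 0.8416·√(0.13·0.87 + 0.078·0.922)]² / 0.052²
= [1.96·0.4317 + 0.8416·0.4301]² / 0.002704 = 1.2081² / 0.002704 ≈ 539.8, so 540.

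The stated 1080 reproduces exactly, and power at 540 per arm is 80.0%. Expected events are 540 × (0.13 + 0.078) ≈ 112.

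**2. Power gained by stratifying on ICU.** Assumptions not in the documents: patients split 17:10 in line with beds (680 and 400), the overall control rate stays at 13%, and the 40% relative reduction is the same in both units. With weight w = 17/27 and m the mean of the two arms' rates within a unit, the stratified null variance is

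V = w·2·m_A(1 − m_A) + (1 − w)·2·m_B(1 − m_B),

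against 2·0.104·0.896 = 0.18637 unstratified. At control rates of 16% and 7.9%, m_A = 0.128 and m_B = 0.0632. Then V = 0.6296·0.22323 + 0.3704·0.11841 = 0.1844, a ratio of 0.9895.

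**3. Chance imbalance without stratified allocation.** With 680 and 400 patients and 540 per arm, the number of first-unit patients in one arm is hypergeometric:

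variance = 540·0.6296·0.3704·(540/1079) = 63.0, SD 7.94.

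The between-arm difference in unit share has SD 2·7.94/540 = 2.94 points, with a 95% range of ±1.96·2.94 = ±5.76 points. The crude difference moves by that imbalance times the between-unit gap in rates, averaged over the two arms. At 16% versus 7.9% the gaps are 8.1 points (control) and 4.86 (TTO), mean 6.48. The shift is 0.0576·6.48 = 0.37 points.

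| Control rates by unit (assumed) | Variance ratio | Power, stratified | Mean gap (points) | 95% shift in crude difference (points) |
|---|---|---|---|---|
| 13% / 13% | 1.000 | 80.0% | 0 | 0 |
| 15% / 9.6% | 0.995 | 80.2% | 4.32 | ±0.25 |
| 16% / 7.9% | 0.989 | 80.4% | 6.48 | ±0.37 |
| 18% / 4.5% | 0.971 | 81.2% | 10.8 | ±0.62 |

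The target difference is 5.2 points. With no treatment effect the full control gap applies, and the 16% / 7.9% row becomes 0.0576·8.1 = 0.47 points. The standard error of the crude difference is √[(0.1131 + 0.0719)/540] = 1.85 points.

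**4. Age bands.** Age is assumed normal with mean 60 and SD 17, truncated to 18–95. Ten-year bands then keep 96.7% of its variance.

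**5. Simulation.** 1500 trials of 1080 patients were run per scenario, with age odds ratios of 1.2 and 1.5 per SD and ICU odds ratios of 1.0, 1.65 and 2.72 (all assumed). Differences in power:

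- Continuous age against an ordered band score: −0.3 to +0.3 points.
- Continuous age against categorical bands (collapsed to six): −0.8 to +0.3 points.
- Continuous age plus ICU against categorical bands without ICU: −0.3 to +0.7 points.

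The simulation error of one power estimate is √(0.8·0.2/1500) ≈ 1 point. Type I error was 0.050 to 0.057 under all the models.

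**The case against.** **The article condenses a fuller plan.** Centre terms and covariate coding often sit in the SAP, which is not shown and may add unit. That would decide the matter if the article were silent. It is not: it gives a specific list, explains some omissions from it, fixes the age bands, and names an unstratified test. It is silent on stratified randomisation, and no fault is claimed there.

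**The list may be only patient risk factors.** On this reading a design factor such as unit would not be expected in it. That is fair, but no other place in the article brings unit into the analysis.

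**The effect is trivial.** This largely stands. At 16% versus 7.9%, unit imbalance accounts for about 1% of the variance of the crude difference, and the ordinary standard error already covers it. If the unit rates are equal, the gain is zero.

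**The age point is preference.** Mostly right. The article does not say whether bands enter as categories or as an ordered score, so a parameter cost is not established. A single continuous term also assumes linearity on the model scale.

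**Readings that go too far.** A reader might infer that baseline information in general goes unused. It does not: age, comorbidities and admission severity are all named, and severity may capture part of the difference between units.

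A reader might also infer that PCR removes extra carriers in Belfast only, so that the outcome means different things in the two units. The documents do not settle this. The exclusion criteria remove patients found positive by standard culture, while the data collection section removes those positive by either method. That conflict needs its own reconciliation and cannot support this point.

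**Conclusion.** The point holds at low severity. The stated covariates omit ICU, the named test is unstratified, and age is banded, in a trial whose two units differ by its own description and whose planning rate comes from one of them.

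It would be wrong to conclude that the primary comparison is biased or the trial undersized. Individual randomisation protects the comparison, simulated type I error stays near 5% with or without the change, and 1080 is reproduced and unaffected.

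What is lost is 0 to about 1 point of power and some protection against chance imbalance: a 95% shift of 0 to about 0.6 points under the planned effect, against a target of 5.2. Both figures depend on the assumed 17:10 split and unit rates. The imbalance figure also assumes unstratified allocation. Unbanding age recovers about 3% of its variance under the assumed age distribution, with no detectable gain in power.

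**What to change.** Under Hypothesis 1: TTO evaluation:

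- State that the primary comparison is stratified by ICU, by a Cochran-Mantel-Haenszel test or by logistic regression with ICU as a term. A Mantel-Haenszel risk ratio stays on the scale of the planned 40% reduction; logistic regression yields a conditional odds ratio, so the effect measure should be named.
- Restrict any adjusted primary model to baseline covariates: ICU, age, comorbidities and admission severity. Antibiotic-days, catheter-days and length of ICU stay accrue after allocation and may be affected by treatment or by colonization. Adjusting for them can bias the effect, so adding ICU while keeping them would not give a sound model.
- Enter age as a continuous term.
- Report results by ICU descriptively.

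The cost is a change of wording. No new data are needed, since unit and age are already known, and the sample size does not change. As the trial is open-label, the change should be dated before any comparative outcome data are seen.
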